### Ethics Approval and Consent to Participate

This study was approved by the Ethics Committee (decision 218/19-03-2019) and the Scientific Board (decision 329/02-04-2019) of the University Hospital of Patras, Greece. The study was registered with ClinicalTrials.gov under the number NCT04163146 (registered on November 14, 2019). Informed consent from parents, or from parents and participants (in the case of adolescents older than 12 years of age), will be obtained at inclusion. The informed consent grants access to the participants’ measurements and medical files, and permits the transmission of data through the internet, given that all conditions of anonymity and data protection are met.

### Lung Function Measurements

PEF and FEV1 measurements will be performed using an FDA-approved ultraportable spirometer (Spirobank Smart; MIR Medical International Research), with a bidirectional digital turbine (flow range ± 16L/s; volume accuracy ±3% or 50 mL; flow accuracy ±5% or 200 mL/s; dynamic resistance <0.5 cm H_2_O/L/s) and capable of connecting to a smartphone via Bluetooth using a dedicated freeware app (iSpirometry, MIR Medical International Research). Apart from PEF and FEV1, the device provides data on the forced expiratory capacity (FVC) and forced expiratory flow between 25% and 75% of FVC (FEF25-75). The app includes graphic incentives to assist in performing technically acceptable tests; it also includes a quality grading system that generates messages to inform whether the measurement was technically correct or, if not, the nature of the mistake (eg, “good blow” for an acceptable test, or “blow faster,” “blow longer,” etc, for nonacceptable maneuvers). Each participant will receive his personal spirometer, which will be paired to one or more smartphones (participant’s device, parents’ device, or both). In a case of two or more participants from the same family, each spirometer will be paired to a separate smartphone. Detailed information regarding use and maintenance of the device will be provided in the form of a printed brochure and online resources available on the study web site [17].

### Protocol

Tests will be performed according to American Thoracic Society/European Respiratory Society (ATS/ERS) standards [18]. The technique will be demonstrated by one of the investigators at enrollment, while detailed information will also be available through the online video resources on the study web site [17]. Measurements will be performed twice a day between 7 AM and 9 AM and between 7 PM and 9 PM. Each participant must perform at least 3 technically acceptable maneuvers. Completed measurements will be dispatched by the participants or their parents to a central database via email (encrypted pdf format).

Eligible children and adolescents will initially be asked to complete a run-in period of 10 days (20 trials) to assess their ability to perform technically acceptable spirometries (daily and at predetermined time frames), dispatch the measurements to the central database, and comply to investigators instructions. Those who will demonstrate satisfactory adherence will proceed to the main study consisting of daily measurements at predetermined time frames for a period of 3 months (90 days, 180 trials).

The expected duration of the study is 24 months and it will include two phases: Phase I and Phase II. Phase I will proceed from January 2020 to September 2020 and will consist of assessments of lung function variability in healthy children and adolescents. Phase II will proceed from October 2020 to December 2021 and will consist of assessments of lung function variability in children and adolescents with asthma.

A flow chart of the study is presented in Figure 1. The protocol is in accordance with SPIRIT (standard protocol items: recommendations for interventional trials) guidelines (Figure 2).

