## Methods

### Study Objectives and Hypotheses

The first objective of the study (objective 1) is the assessment of lung function variability in healthy children and adolescents, focusing on the range and pattern of short- and long-term fluctuations of PEF and FEV1 and the parameters that may influence them. The second objective (objective 2) is the assessment of lung function variability in children and adolescents with asthma; the pattern of short- and long-term PEF and FEV_1_ variability will be established and the differences from healthy subjects will be defined. Specific changes in the variability pattern prior to exacerbation will also be sought and described (objective 3).

We hypothesize that healthy children and adolescents present normal short- and long-term variability of PEF and FEV1, and that the pattern of variability is influenced by age, sex, and environmental stimuli (season, weather conditions, viral infections, etc). Significant lung function variability is also expected for children and adolescents with asthma; the patterns of variability in children and adolescents with asthma may differ from those observed in healthy children and adolescents, being also influenced by environmental conditions and treatment modalities (controller therapy) in a distinguishable way. Finally, we hypothesize that changes in the pattern of lung function variability occur prior to the loss of asthma control and, thus, may be used to predict the exacerbations of the disease.

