### Sample Size Estimation

Data regarding long-term PEF and FEV1 variability in children and adolescents (with or without asthma) are lacking. Based on lung function variability, data from adults with asthma [14], and assuming a maximum dropout rate of 10%, we estimated that a sample size of 200 children and adolescents (100 in each group) would allow us to detect a difference of at least 1% in PEF or FEV1 coefficient of variation (CV) between healthy participants and participants with asthma, with 90% power at the 0.05 level. Sample size estimation was performed using the G*Power software (version 3.1.6) [15] after assuming a nonparametric distribution of lung function parameters (Wilcoxon rank-sum test).

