## Results

The study is funded by the “C. Caratheodory” Programme of the University of Patras, Greece (PN 47014/24.9.2018). It was approved by the Ethics Committee (decision 218/19-03-2019) and the Scientific Board (decision 329/02-04-2019) of the University Hospital of Patras, Greece.

Patient recruitment commenced in January 2020, and the trial is scheduled to end in January 2022. As of June 2020, 100 healthy children have been enrolled (74 of them have completed the measurements). The anticipated duration of the study is 24 months. The first part of the study, the assessment of lung function variability in healthy children and adolescents, will be completed in August 2020, and the results will be available for publication by October 2020.

Access to the study dataset will be limited to the investigators. After the analysis and publication of the results, the study database will be made available by the corresponding author upon reasonable request. Results will be published in peer-reviewed journals and will be presented in relevant conferences. Authorships will follow the Vancouver declaration.

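### The two cohorts are measured in successive, non-overlapping periods, so the objective 2 group difference is partly confounded with season and fully confounded with calendar period

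*Protocol article*

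**What the plan says.** The Protocol section sets two consecutive phases. For the healthy cohort, "Phase I will proceed from January 2020 to September 2020"; for the asthma cohort, "Phase II will proceed from October 2020 to December 2021". After a 10-day run-in, each child provides "daily measurements at predetermined time frames for a period of 3 months (90 days, 180 trials".

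Study Objectives and Hypotheses makes the between-group contrast part of objective 2: "the differences from healthy subjects will be defined". The same section hypothesizes for healthy children that "the pattern of variability is influenced by age, sex, and environmental stimuli (season, weather conditions, viral infections, etc", and for children with asthma that the patterns may differ, "being also influenced by environmental conditions and treatment modalities (controller therapy) in a distinguishable way".

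Sample Size Estimation rests on the same contrast: the aim is to "detect a difference of at least 1% in PEF or FEV1 coefficient of variation (CV" between the groups, with 90% power at the 0.05 level and at most 10% dropout.

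The Results section reports progress: "As of June 2020, 100 healthy children have been enrolled (74 of them have completed the measurements". It expects the healthy part to be complete in August 2020.

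The Statistics section compares the groups by t test or Mann-Whitney U test. It plans multivariable linear regression only as an exploration of unnamed parameters.

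**The concern.** Each child is observed for about one season, and cohort membership determines which seasons are available. The plan thus ties group to a factor that it expects to alter the outcome, and the stated two-sample tests do not separate the two. At stake is objective 2, the comparison on which the study was sized. Part of any observed difference in CV, DFA slope or sample entropy could reflect when the children were measured rather than whether they have asthma.

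The healthy calendar can no longer change, because all 100 children are enrolled. On the article's dates the asthma phase had not begun, so its schedule and the form of the comparison could still be set.

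**Working it through.** **1. Calendar overlap (Protocol section dates).** Phase I covers 9 months and Phase II covers 15. They share no month of real time, so calendar period is completely confounded with group.

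By month of the year:
- October-December: 0 of 9 healthy months and 6 of 15 asthma months (40%).
- If healthy measurement ends in August, September also has no healthy data: 7 of 15 (47%).
- January-September: present in both phases, in 2020 and 2021 respectively. Confounding with season is therefore partial.

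**2. Person-days rather than months.** Assume that enrolment is uniform over the days on which 10 + 90 days still fit inside the phase. Phase II has 457 days, hence 457 − 100 + 1 = 358 possible enrolment days. Counting the 90 measurement days for each start gives:

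| Share of person-days | Healthy | Asthma |
|---|---|---|
| October-December | 0% | 23.8% |
| April-July | about 67% | about 34% |

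The 24% is below the 40% of calendar months because October 2020 and December 2021 lie at the ends of the phase, where few windows are open. The true healthy distribution is probably more concentrated than uniform: recruitment began in January 2020 and 74 of 100 had finished as of June, so those windows lie wholly within January-June.

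**3. Planning SD.** The article gives no SD of CV, so the sample size cannot be reproduced forwards. Solving backwards, with two-sided 0.05, 90% power and a difference of 1 point:
- n = 2 × (1.960 + 1.282)² × SD² / 1². With SD = 2.0 this is 84.1, so 85 per group.
- Wilcoxon efficiency 3/π = 0.955: 85 / 0.955 = 89.0, rounded up to 90.
- Dropout: 90 / 0.9 = 100 per group, as stated.

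The stated size is attainable with an SD of about 2.0. Depending on conventions, the implied SD is 1.9-2.2 two-sided.

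**4. Illustrative bias.** Assume no true disease effect, 90 analysed per group, and a CV raised by e points in October-December only. For exactly 90 per group the implied SD is 2.02.
- SE = 2.02 × √(2 / (90 × 0.955)) = 0.308.
- Bias = e × (share in asthma − share in healthy) = e × 0.238.
- Type I error = Φ(bias/SE − 1.96) + Φ(−bias/SE − 1.96).

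| Assumed effect e (CV points) | Bias (CV points) | Type I error |
|---|---|---|
| 0.5 | 0.12 | 7% |
| 1 | 0.24 | 12% |
| 2 | 0.48 | 34% |

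**5. Room for rescheduling.** January-September 2021 has 273 days, so 273 − 90 + 1 = 184 starts keep all 90 measurement days inside it. If healthy data end in August, 243 − 90 + 1 = 154 do. Under uniform enrolment over Phase II, (358 − 184) / 358 = 49% of asthma children would have some October-December data.

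**The case against.** **The amount of confounding.** A reader might infer that every seasonal effect passes into the group difference. The documents do not support that: Phase II covers all twelve calendar months, so season can be adjusted for, or matched, in January-September. This stands, and the confounding with season is partial. Confounding with calendar period is not.

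**The size.** A reader might take 40% of asthma data as lying in October-December. With a 1-point effect that would give a 0.40-point bias and about 25% type I error. But 40% is a share of months, not of child-time; uniform enrolment gives 24% and a type I error of 12%. Even that assumes an effect as large as the whole planned group difference, and the SD is back-solved. The illustration also treats January-September as flat. Healthy data lean towards winter and spring, so the sign of the net bias is unknown.

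**The plan's claim about season.** It would be too strong to say that the plan declares season to drive variability. It hypothesizes an influence.

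**Analysis detail.** Values are stored by date and time (Data Acquisition and Monitoring), and the planned regression could include season; an article may leave covariate lists to the full protocol. That is fair, and the absence of a covariate list is not the finding. The finding is the stated phase calendar combined with the stated unadjusted comparison. No analysis plan can supply healthy data for October-December.

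**Scope.** Objective 1, and objective 3 as a within-asthma question, are not affected by this between-group confounding.

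**Conclusion.** The concern holds for objective 2. By design, the healthy-versus-asthma difference is partly confounded with season and fully confounded with calendar period, and the group tests in the Statistics section account for neither. The calendar facts come directly from the article. The 24% share assumes uniform enrolment. The bias of about 0.12-0.24 CV points and type I error of about 7-12% further assume an October-December effect of 0.5-1 point, an SD of about 2.0 and 90 analysed per group. These show scale only; the documents fix neither the magnitude nor the direction. Seasonal confounding can be reduced with data already to be collected. Confounding with calendar period, including period-specific viral circulation, remains under any fix.

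**What to change.** 1. **Comparison.** Make the objective 2 analysis a regression of CV, and of the DFA and sample entropy indices, on group, adjusted for the calendar month or season of each child's window. The stored measurement dates suffice. Because windows span several months, the share of measurement days in each month or season is a natural coding.
2. **Sensitivity analysis.** Repeat the comparison with only those asthma children whose windows lie in months with healthy data. This avoids extrapolating to October-December. It also matters because the plan expects environmental influence to differ in asthma, so one common seasonal term may not fit both groups.
3. **Scheduling, where feasible.** Concentrate asthma windows in January-September 2021 so that they mirror the healthy month distribution. Use October-December windows for the asthma-only description and objective 3.
4. **Interpretation.** State that differences between calendar periods (2020 against 2020-2021) cannot be separated from group, and limit the objective 2 conclusion accordingly.

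**Cost.** Items 1 and 4 need no new data. Item 2 uses fewer children and so loses precision: under uniform enrolment about 49% of asthma children would fall outside a January-September restriction. Truncating their series instead would shorten the input to the 24 moving CV windows and to DFA. Item 3, applied in full, roughly halves the usable enrolment period, to 184 of 358 days (154 if healthy data end in August). Exact mirroring would be tighter still, since most healthy windows closed by June. Full mirroring may therefore be out of reach, and items 1 and 2 should be specified in any case.

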**Figure 1 figure1:**
[figure not shown]
Study flow chart.

**Figure 2 figure2:**
[figure not shown]
Standard protocol items: recommendations for interventional trials (SPIRIT) checklist.

### Data Acquisition and Monitoring

PDF files will be downloaded and converted to text files using optical character recognition. PEF, FEV1, FVC, and FEF25-75 values, as well as quality grading of each measurement, will be recognized and introduced in a specific registry. The best PEF, FEV1, FVC, and FEF25-75 values among the technically acceptable trials for a given date and time will be identified and transferred from the registry to a participant-specific file. Additionally, all registry data will be included in a monitoring table that presents the number of acceptable tests per day and time for each participant (Figure 3). PDF downloading and data acquisition will be performed automatically by special scripts implemented in MatLab (version R2019a; MathWorks Inc).

The monitoring table (Figure 3) will be reviewed twice a day (at 11 AM and 11 PM) and participants will be notified by direct telephone contact in case of inappropriate technique or missing measurements.

**Figure 3 figure3:**
[figure not shown]
Example of the monitoring table presenting the number of acceptable tests per day/time point for each participant. Green cells: full adherence; orange cells: <3 acceptable measurements; red cells: missed measurements.

### Variability Analysis

Participant-specific files will be used for variability analysis, focusing primarily on the variability of PEF and FEV1 and secondarily on FEV1/FVC and FEF25-75. All variables will be transformed into percentage predicted values according to GLI normative data [16].

Lung function variability will be assessed in 3 ways: (1) standard variability indices, (2) detrended fluctuation analysis (DFA), and (3) sample entropy (SampEn).

Standard variability indices such as CV (defined as SD divided by the mean) will be used. To avoid any bias due to the presence of trends within the time series, CV will also be calculated as the average of 24 moving windows (length 14 measurements; step 7 measurements).

DFA is a method that has been widely used for the investigation of intrinsic correlation within time series [19]. Initially, the square root of the time series F(*n*) is calculated for segments of different (time) length *n*. A linear relationship in the logarithmic graph F(*n*) - log(*n*) indicates the existence of fractal architecture in the scaling of the specific data, while the slope *a* of the line describes the pattern of long-term fluctuations [19]. A change in daily variability of PEF or FEV1 results in a simultaneous deviation from the predetermined *a* value [6]. This deviation can easily be detected and quantified. It has been shown that the magnitude of *a* deviation reflects the likelihood of asthma exacerbation within the next month [6].

SampEn is a measure of increased irregularity or complexity, which relies on the identification of recurrent patterns within a nonstationary time series (ie, the probability that a series of points within the signal will repeat themselves at a subsequent time-point) [20]. Within a regular and less complex system, the frequency of sequence matches is high; therefore, the entropy is low. SampEn has emerged as a more reliable index of dynamic variability, mainly because it is relatively independent of the length of the time series [20].

Variability analysis will be performed in the MatLab environment.

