## Introduction

Asthma is the most common chronic disease of childhood and represents an important cause of morbidity worldwide [1]. The disease is characterized by episodes of reversible airway obstruction (exacerbations), with specific symptoms (such as wheezing, dyspnea, coughing, chest tightness) and a decrease in peak expiratory flow (PEF) and forced expiratory volume at 1 second (FEV1) [2]_._ However, lung function changes occur in parallel with clinical deterioration, thus presenting limited ability to predict the exacerbation of the disease [3].

Both PEF and FEV1 demonstrate significant daily variability, in relation to circadian and day-by-day fluctuation of measured values [4,5]. In healthy individuals, the pattern of these fluctuations remains constant over long time periods (weeks or months); this contrasts with patients with asthma, for whom PEF and FEV1 variability increase with loss of disease control, especially prior to exacerbations [5,6]. Thus, lung function variability analysis has been used in research to recognize high-risk patients, predict asthma exacerbations, and evaluate the effectiveness of treatment [6-10].

In clinical practice, however, the evaluation of lung function variability requires daily measurements with portable devices, the recording of PEF and FEV1 values in specialized diaries, and periodic evaluations of the data by the attending physicians [2]. The whole process may be both complicated and time-consuming, reducing patients’ adherence—especially in the cases of children and adolescents [11,12]. In addition, the periodic post hoc review of measurements may hamper the prediction of exacerbations, as the time of evaluation may not coincide with changes in the variability of lung function that characterize the loss of asthma control [12].

In recent years, technological advancements in the field of biosensors and microprocessors have permitted the development of reliable, low-cost, ultraportable spirometers, able to connect with cutting-edge mobile phones (smartphones) and monitor lung function parameters in real time and from a distance [13]. The introduction of such devices in clinical practice may overcome most of the aforementioned barriers in following up lung function parameters in the long term [13].

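### DFA and SampEn appear to run on one alternating morning/evening series, so a group difference in day-night swing relative to noise can shift the DFA slope, which the plan reads as long-term pattern

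*Protocol article*

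**What the plan says.** The Protocol section sets the schedule: "Measurements will be performed twice a day between 7 AM and 9 AM and between 7 PM and 9 PM", "for a period of 3 months (90 days, 180 trials"). Under Data Acquisition and Monitoring, the best values "among the technically acceptable trials for a given date and time will be identified and transferred from the registry to a participant-specific file". The Variability Analysis section then says "Participant-specific files will be used for variability analysis" and names three methods: "Lung function variability will be assessed in 3 ways: (1) standard variability indices, (2) detrended fluctuation analysis (DFA), and (3) sample entropy (SampEn").

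For the coefficient of variation (CV), "CV will also be calculated as the average of 24 moving windows (length 14 measurements; step 7 measurements"). The stated purpose of these windows is to guard against trends. No separation by time of day, daily averaging or removal of a morning-evening difference is described for any method.

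The same section says that the DFA slope *a* "of the line describes the pattern of long-term fluctuations", and it reads low SampEn as a sign of a regular, less complex system. The Introduction acknowledges the component at issue: "Both PEF and FEV1 demonstrate significant daily variability, in relation to circadian and day-by-day fluctuation of measured values". Objectives 1 and 2 ask for both short- and long-term fluctuation.

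**The concern.** With two readings a day, a fixed difference between a child's morning and evening level is an oscillation that repeats every two points. It belongs to the shortest time scale in the data. The DFA slope is fitted across box sizes from short to long, so whatever raises fluctuation only in the short boxes tilts the line.

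If children with asthma have a larger morning-evening swing relative to their day-to-day noise than healthy children, their slope will be lower even when day-to-day dynamics are identical. Under the plan's reading, that would be reported as a different long-term pattern. The comparison of groups is Objective 2, and Objective 3 looks for changes in the same indices before exacerbations. A diurnal difference may well be a genuine and useful result, but it should be reported as diurnal.

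**Working it through.** **1. The plan's own figure.** Number of windows = floor((N − 14)/7) + 1.
- N = 180 (morning and evening interleaved): (180 − 14)/7 = 23.7, so 23 + 1 = 24, as stated.
- N = 90 (mornings only, evenings only or daily means): (90 − 14)/7 = 10.9, so 10 + 1 = 11.
- Only N from 175 to 181 gives 24.

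So CV uses the interleaved series. Each window of 14 holds 7 morning and 7 evening values, and windowing leaves the swing in. For DFA and SampEn, pooling is inferred from the shared file and the absence of any split.

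**2. Why the slope moves.** Let D be the morning-evening difference and A = D/2. A series alternating between +A and −A has a cumulative sum that alternates between two levels A apart. It adds about A²/4 to the squared fluctuation F²(n), whatever the box size n. With D in % of the mean:
- D = 2.5: 1.25²/4 = 0.39
- D = 5: 2.5²/4 = 1.56
- D = 10: 5²/4 = 6.25

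The noise part grows roughly as n^(2H). With H = 0.7, from n = 4 to n = 45 it grows by about (45/4)^1.4 ≈ 30-fold. A constant added to a growing quantity matters most in small boxes, so the fitted line flattens.

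**3. Size for one series.** Inputs not in the documents are assumed: fractional Gaussian noise, residual SD 5% of the mean, 180 points, boxes 4-45, SampEn with m = 2 and r = 0.2 SD.

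| Swing, % of mean | A / residual SD | DFA slope | SampEn |
|---|---|---|---|
| 0 | 0 | 0.726 | 2.19 |
| 2.5 | 0.25 | 0.710 | 2.19 |
| 5 | 0.50 | 0.671 | 2.18 |
| 10 | 1.00 | 0.562 | 1.85 |

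The slope differs by 0.710 − 0.671 = 0.039 for 2.5% vs 5%, and by 0.671 − 0.562 = 0.109 for 5% vs 10%. A further run placed SampEn at about 2.17 without a swing, 2.04 at a 7.5% swing and 1.85 at 10%.

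The slope result does not hang on one noise model. At swings of 0, 8 and 15% it was:
- white noise: 0.53, 0.45, 0.33
- AR(1) noise: 0.90, 0.76, 0.59
- H = 0.8: 0.83, 0.68, 0.51
- H = 0.8 with boxes 10-45 only: 0.79, 0.72, 0.60

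**4. Size for the group comparison.** Mann-Whitney test on the slope, 90 vs 90 (100 per group less the plan's 10% dropout), same long-range structure in both groups, H = 0.7:

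| Swing, healthy vs asthma | False rejection, raw series |
|---|---|
| Equal swing-to-noise ratio | about 5% |
| 1% vs 2% | about 4-11% |
| 2.5% vs 5% | about 62-94% |
| 5% vs 10% | 100% |

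In the third row the upper figure gives every child the same swing and scaling exponent; the lower one lets children differ. The lower end depends on how much spread is assumed: an SD of 0.1 in the exponent alone gave 73% in one run, and adding an SD of 0.25 residual SDs in the swing gave 53%.

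**5. After centring.** With each child's morning and evening means subtracted from the 180-point series, rejection was close to the nominal 5%. Runs of 60 simulated trials gave 2-13%; their Monte Carlo standard error at 5% is √(0.05 × 0.95/60) = 2.8 points. At H = 0.8 the centred slope stayed at 0.82-0.83 and SampEn at 2.08-2.12 for every swing from 0 to 15%.

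**The case against.** The strongest reply is that the day-night swing is part of what the study sets out to measure. The objectives include normal daily fluctuation, the Introduction counts circadian change as variability, and the Variability Analysis section itself says that a change in daily variability moves *a*. This stands for CV: a larger swing that raises CV is real variability. It does not rescue the reading of the slope. If *a* responds to daily variability, it cannot by itself describe long-term pattern.

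A second reply is that the size is unknown. This stands. The DFA slope, and SampEn with a tolerance set as a fraction of the SD, do not change when a whole series is rescaled. If asthma raises swing and noise in proportion, there is no artefact.

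A third is that box sizes, SampEn settings and pre-processing may sit in a fuller document. Their absence here is not the point; the stated window count, the shared file and the stated reading of *a* are.

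A reader might also infer more than the documents support:
- **That pooling is stated for all three methods.** The window count proves it for CV only.
- **That SampEn is as exposed as DFA.** At 2.5% vs 5% it is 2.19 vs 2.18.
- **That SampEn needs detrending because a trend lowers it.** A visible effect was shown only for a drift of 4 residual SDs, which is 4 × 5% = 20% of the mean over three months. Nothing in the documents supports that size.
- **That asthma will show the larger swing-to-noise ratio.** The protocol gives no figures on this.

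**Conclusion.** The point holds for the DFA slope and, at large swings only, for SampEn. The pooled series is certain for CV and the natural reading for the other two methods. A group difference in swing relative to noise can then be mistaken for altered long-term structure. How likely that is depends on quantities the documents do not give: under the assumptions above, the chance of a false difference in slope runs from the nominal level to certainty. The range is the finding, and no single rejection rate should be quoted as the risk in this trial. It is a cheap improvement to the analysis and does not call the data collection into question.

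**What to change.** In the Variability Analysis section, add that DFA and SampEn will also be computed after subtracting each child's own morning mean and evening mean from the full 180-point series, and that statements about long-term pattern or complexity will rest on this centred version. Keep the raw-series values for comparison with the adult literature. Report the morning-evening difference, as a percentage of the child's mean, as a separate short-term index.

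Separate morning and evening series should not be treated as equivalent. They also remove the swing, but leave 90 points and 11 windows and give different values (H = 0.8: slope 0.75-0.77 and SampEn 2.23-2.27, against 0.82-0.83 and 2.08-2.12 when centred).

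The cost is a few lines of script, a short addition to the text and one extra set of DFA and SampEn results. No new data are needed. The downside is that the centred values are less directly comparable with published pooled-series values, which is why the raw values stay.
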